#### Management and analysis of formative data

##### Qualitative analysis

All interviews and focus groups will be conducted by trained study personnel, audio-recorded, transcribed verbatim, and imported into qualitative data management software for analysis. Initially, one researcher will read and code each transcript by question, and conduct rapid analysis to inform the intervention. Subsequently, two researchers will read each transcript, create and apply an initial codebook based on the questioning structure to a subset of the data. Following this, researchers will meet to discuss emerging themes, check inter-coder reliability, resolve discrepancies, and create a consensus codebook. Data then will be recoded using the revised codebook, and key themes will be reviewed and discussed.

##### Choice experiment analysis

In addition to the audio-recording, the choice experiment exercise completed by low-income adults and full-paying CSA members will be detailed with hand-written notes, which will be used to inform the development of the coding schema. Each participant will be assigned a “willingness to shop or buy” score based on number of times they said “yes” to each purchasing situation. Frequencies and percentages of participants willing to utilize CSAs for each price/accessibility situation will be generated. Nominal variables reflecting produce preferences, given frequency, size, and price, also will be tabulated. Results will be examined separately by race/ethnicity, geographic region, and household size. Researchers will meet to resolve discrepancies between coding and tabulation.

### Component 2: Examination of dietary outcomes among current CO-CSA participants

To inform the randomized trial (component 4) and explore longitudinal diet patterns among CO-CSA families with children, we are partnering with the Northeast Organic Farming Association of Vermont (NOFA-VT) to conduct a longitudinal quantitative examination of dietary behaviors among applicants to their statewide CO-CSA Farm Share program, which offers a subsidy of up to 50% of CSA share costs. Subsidies are provided on a first-come, first-served basis to households whose self-reported income is ≤185% of the federal poverty level (FPL). Lists of applicants to the summer and winter Farm Share programs will be provided by NOFA-VT, and households with at least one child aged 2–12 years and with an email address will be added to the research panel. Sample size calculations indicated that sixty households are needed to observe significance of a change in consumption of one-third of a serving of vegetables, with 95% confidence, and 80% power.

#### Data collection and outcomes

Using an online questionnaire, we will measure and track CSA participation; household food security; the household’s use of federal food assistance programs; fruit and vegetable availability in the home; and intake of beverages, snacks, and fruits and vegetables (in general and season-specific) by the adult caregiver and one child aged 2–12 years at first contact. Basic information on participant characteristics also will be collected. To inform the intervention, a subset of households will be asked additional questions about the cooking tools they own and the costs associated with participating in a CSA, and will be invited to complete three non-consecutive dietary recalls (2 week days and one weekend day) for the child using the Automated Self-Administered 24-h (ASA24) system [73]. Beginning in Year 1, data will be collected quarterly.

#### Analysis

Summary statistics will describe CO-CSA participant characteristics, food access and use of food assistance, as well as experience with CSAs. Mean total fruit and vegetable intake among CO-CSA participants will be compared to age-sex specific recommendations, and to national averages, using paired t-tests. Intake of fruits and vegetables, and of snacks and sugar-sweetened beverages, across two points in time will be compared using paired t-tests. In-season and out-of-season consumption of particular fruits and vegetables will be contrasted using nonparametric tests.

### Component 3: Develop skill-based, CSA-tailored education curriculum

The development of a CSA-tailored, skill-based nutrition education curriculum will be informed by components 1 (formative research) and 2 (longitudinal analysis). A curriculum advisory committee composed of extension education representatives from each of the four states will provide input and feedback throughout the curriculum development process. Information from existing EFNEP and Supplemental Nutrition Assistance Program Education (SNAP-Ed) curricula will be adapted and integrated, as appropriate.

Social Cognitive Theory [74], the Dietary Guidelines for Americans [75], and the Physical Activity Guidelines for Americans [76] will guide the design of learning objectives, education strategies and activities. The overarching objectives of the education will be to: (1) address attitudes and beliefs about the value of consuming fruits and vegetables (outcome expectation); (2) improve skills and self-efficacy with respect to storing, preparing, and consuming CSA produce (self-efficacy); (3) reduce potential barriers to acceptance of CSA produce and develop strategies to substitute fruits and vegetables for more energy-dense foods (barriers); (4) increase skills and self-efficacy related to preparation of CSA produce using minimal solid fat and sugar (behavioral capacity); (5) provide opportunities for participants to observe peers demonstrating newly acquired skills and share new experiences via group discussion (observational learning/modeling); and (6) provide information and strategies to help families be more active in daily life and reduce sedentary time, particularly screen time.

The curriculum will be composed of nine lessons, with three relevant to the early CSA season, three relevant to the middle of the CSA season, and three relevant to the late CSA season. Lessons will be modeled using the 4A Approach [77]: a beginning “anchor” activity will ground participants’ learning in their current knowledge and behaviors related to the lesson’s topic; the educator will “add” to current knowledge by providing participants’ with information on and demonstration of new knowledge and skills; participants “apply” what they learn through hands-on activities; and a closing “away” activity will help participants plan how they will use what they have learned in their every-day lives. Most classes will include at least one “apply” activity involving food preparation given the evidence that such experiences may stimulate behavior change, particularly an increase in fruit and vegetable intake [61, 62]. A subset of classes will involve field-based learning (e.g. grocery store and farm tours). Although the education will focus on adults, each lesson will include child-friendly materials and activities. Supportive out-of-class materials also will be developed.

### Component 4: Randomized intervention trial of CO-CSA plus tailored education

Incorporating the findings and products generated in components 1–3 (formative evaluation, longitudinal analysis, and curriculum development), we will implement an exploratory field experiment – the Farm Fresh Foods for Healthy Kids (F3HK) intervention – beginning in Year 2. This multistate randomized intervention trial will target obesity prevention in low-income families through a transdisciplinary approach that improves access to affordable, local, seasonal produce through the provision of a CO-CSA share; supports dietary and other obesity-related behavior changes (e.g. reducing sedentary time) through tailored education to increase knowledge, skills, and self-efficacy; and provides increased revenue and business supports to CSA farmers, which will help support local agricultural economies.

The intervention will be implemented across communities in New York, North Carolina, Vermont, and Washington. A list of specific communities is available at ClinicalTrials.gov. Participants will receive a weekly CO-CSA share at 50% discount and the education curriculum developed in component 3 (curriculum development). The remaining 50% cost will be paid by the study to the farmers upfront. The CO-CSA will fit into existing CSA programs.

Each state will recruit 60 participants within at least two CSA programs. Participants will enroll in the CO-CSA for two seasons and participate in the CSA-tailored education during the first season. We will randomize families into either the intervention or control (delayed intervention) group. Group 1 (intervention) families will participate in the CO-CSA plus tailored education in Year 2 and Year 3; Group 2 (control) families will receive the same CO-CSA plus tailored education in Year 3 and Year 4 (Table 3). A delayed parallel design was selected in order to keep the benefits of participation, and therefore the motivation to keep participating, equivalent for parallel groups. We will work with participating farmers to support the transition to alternative funding for the cost-offset following completion of the intervention. Participants will be asked not to enroll in a CSA outside of the study. Participants may enroll in other nutrition education at any time during the trial. Data will be collected at identical time points for all participants. Bi-annual engagement postcards or letters will be mailed to all participants with the aim of increasing retention.

**Table 3 Tab3:** Delayed intervention design for component 4 (randomized trial)

	Year 2	Year 3	Year 4
Group 1 – intervention	CO-CSA + Education	CO-CSA	Sustainability
Group 2 – control	Data collection only	CO-CSA + Education	CO-CSA
Group 3 – intervention		CO-CSA + Education	Sustainability
Group 4 – control		Data collection only	CO-CSA + Education

In Year 3, to compensate for study attrition, we will recruit additional participants and randomly assign into an identical intervention of shorter duration or control (delayed intervention). Group 3 (intervention) families will participate in the CO-CSA plus tailored education in Year 3 only; while Group 4 families will receive the same CO-CSA plus tailored education in Year 4 only. The study timeline is presented in Fig. 1.

**Fig. 1 Fig1:**
[figure not shown]
Flow of participants in component 4 (randomized trial) from recruitment through the end of the study

#### Farms and educators

We will seek farms with an established CSA program who accept, or are willing to accept, Supplemental Nutrition Assistance Program (SNAP) benefits; are willing to offer weekly payment plans for study participants; and who agree to participate in the creation and implementation of a sustainability plan to keep the CO-CSA program in place at the conclusion of the intervention period. Additionally, there must be a professional community health educator (herein referred to as an educator) in the community who is able and willing to deliver the CSA-tailored curriculum. The educator will also assist the study team in recruiting and screening participants. Educators will have extensive experience working with low-income families and delivering nutrition programming and many will have an affiliation with cooperative extension (https://nifa.usda.gov/extension). Educators will complete an interactive, two-hour, web-based training on the CSA-tailored curriculum, covering the organization and content of the curriculum and a review of best practices for educating adult learners, including tenants of Dialogue-Based Adult Learning and Adult Learning Theory [78–80].

#### Participants

##### Recruitment

Study personnel and educators will recruit participants via flyers, newspapers, websites, and social media, as well as direct recruitment at schools, churches, libraries, community service organizations, local events, and “word of mouth.”

##### Screening and eligibility

Potential participants will be screened for eligibility using an electronic tablet-based screening tool. The eligibility criteria for participation is: (1) age 18 years or older; (2) English-speaking; (3) parent or legal guardian of at least one child between 2 and 12 years of age in the household (herein referred to as a caregiver); (4) meet income requirements of ≤185% of FPL (self-reported); (5) have not participated in a CSA in the past 3 years; (6) be willing to use their SNAP benefits or their own money to purchase the 50% CO-CSA share; (7) have an active email address and access to a computer or tablet for online data collection; and (8) be willing to attend CSA-tailored education classes as part of the intervention.

To enroll into the study, participants must: (1) attend a baseline assessment visit and provide written consent; (2) complete the first online questionnaire; and (3) if assigned to intervention, pay the farm a deposit equal to two weekly CO-CSA payments (refundable at the end of the season if all payments are made). The decision to require a deposit draws on the experiences of a program that provided no-cost CSA shares to low-income consumers in North Carolina, which indicate participants may be more engaged with a CSA arrangement if they make a financial commitment [55].

In each participating household, one caregiver and one child aged 2–12 years (herein referred to as the focal child) will enroll in the study. Caregivers will provide written informed consent to take part and written permission for the focal child to participate. Children 7–12 years will provide oral assent. Consent and assent will be obtained by trained study staff. Any ancillary studies that develop out of this project will obtain participant consent separately. Informed consent materials are available as Additional file 1.

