#### Randomization

Following enrollment and baseline assessment, participants will be 1:1 randomly assigned to intervention and control groups within CSA program communities by trained research staff using a computer-generated randomizer to assure equivalent group sizes at each farm location. Randomization will take place after informed consent is obtained at study enrollment appointments. Given the nature of the intervention, neither the participants nor the study staff will be blinded to group assignment.

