##### Analysis of primary and secondary intervention outcomes

Intent-to-treat analyses will allocate all participants to initial random assignment group for measurement at Year 2 baseline, Year 2 fall assessment, and Year 3 spring assessment. Subsequently, Group 2 will be considered to have received the intervention for measurement at Year 3 fall assessment, Year 4 spring assessment, and Year 4 fall assessment. Likewise, Groups 3 and 4 will maintain initial random assignment for measurement at Year 3 spring assessment, Year 3 fall assessment, and Year 4 spring assessment, but then Group 4 will be considered to have received the intervention for Year 4 fall assessment.

Change variables for linear outcomes (Table 4) will be created by subtracting the baseline from the measurement at the end of the CSA season, as well as during subsequent measurement points. Multilevel linear models with fixed and random effects will be used because observations are repeated measures for participants nested within farm communities. Models also will include intervention group status, baseline measures of outcome variables, and relevant covariates. Additional models will control for CO-CSA and education dose received. Multiple imputation will be used to estimate partial missing data.

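### Payment of a farm deposit is listed as an enrolment condition for the intervention arm only, which contradicts the stated order of randomisation and permits one-sided exclusion after assignment

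*Protocol article*

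**What the plan says.** All references are to Component 4 of the protocol article.

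- **Screening and eligibility.** The enrolment list opens "To enroll into the study, participants must: (1) attend a baseline assessment visit and provide written consent", continues with the first online questionnaire, and ends with "if assigned to intervention, pay the farm a deposit equal to two weekly CO-CSA payments". The deposit is refundable at the end of the season if all payments are made. The reason given is experience from a no-cost CSA programme in North Carolina, which suggested that a financial commitment may make participants more engaged.
- **Randomization.** "Following enrollment and baseline assessment, participants will be 1:1 randomly assigned to intervention and control groups within CSA program communities". The section adds that "neither the participants nor the study staff will be blinded to group assignment".
- **Analysis of primary and secondary intervention outcomes.** "Intent-to-treat analyses will allocate all participants to initial random assignment group". On missing values: "Multiple imputation will be used to estimate partial missing data".

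No section says whether an assigned household that does not pay the deposit is kept, followed up or analysed.

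**The concern.** An enrolment condition that names the assigned arm can operate only after assignment. Here it operates in one arm, and control households face no counterpart. If membership of the study depends on it, the people counted as participants are fixed by an act that follows randomisation and that households choose knowing their arm.

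The intent-to-treat sentence covers participants, not all randomised households. A non-payer who by the enrolment list never enrolled has no clear place in it. Imputation of partial missing data does not clearly reach a household with no follow-up at all.

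The households that drop out at this step are unlikely to be a random subset. Income is at or below 185% of the federal poverty level, the Background says that upfront payment may deter low-income families, and the deposit was adopted because payment is thought to go with engagement. If non-payers were removed from one arm, the comparison would lose the protection that randomisation gives.

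**Working it through.** **1. Order of steps.** Set side by side:

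| Section | Order implied |
|---|---|
| Screening and eligibility | consent and baseline visit, questionnaire, *assignment*, deposit (intervention only), enrolment complete |
| Randomization | enrolment and baseline complete, *assignment* |

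For control households the two can agree. For intervention households they cannot, because enrolment would have to be complete before an assignment on which its third condition depends.

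**2. Who is analysed.** If the enrolment list governs, intervention non-payers are not participants and the intent-to-treat sentence does not reach them. If the Randomization section governs, they are enrolled and the deposit is only a step in taking up the share. The article does not say which.

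**3. Numbers from the plan.** The point rests on no stated figure, but the illustration needs a number analysed. The plan has 120 households per arm and 25% attrition, so 120 × 0.75 = 90 per arm. As a check on the planned 240: a 0.5 SD effect with two-sided 5% (sidedness assumed) and 80% power needs 63 per arm, 126 in total. With 10 households per arm in each community and an intra-class correlation of 0.05, the design effect is 1 + 9 × 0.05 = 1.45. Then 126 × 1.45 = 183 and 183 / 0.75 = 244, close to 240.

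**4. Bias if non-payers were excluded.** Let f be the share of the intervention arm not paying, and d the amount, in SD, by which their outcome change would fall short of payers' with no intervention effect. The mean of the full arm is (1 − f) × P + f × (P − d) = P − f × d, where P is the payers' mean. Keeping payers only shifts the contrast by **f × d**.

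**5. Type I error.** Analysed: 90 control and 90 × (1 − f) intervention. SE = √(1/90 + 1/[90(1 − f)]). Rejection probability = Φ(−1.96 + f × d/SE) + Φ(−1.96 − f × d/SE). Both f and d are assumed, since the document gives neither.

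| f | d (SD) | bias (SD) | share of 0.5 SD target | n intervention | type I error |
|---|---|---|---|---|---|
| 5% | 0.2 | 0.01 | 2% | 85.5 | 5.1% |
| 10% | 0.5 | 0.05 | 10% | 81 | 6.2% |
| 20% | 0.5 | 0.10 | 20% | 72 | 9.7% |
| 30% | 0.5 | 0.15 | 30% | 63 | 15.0% |

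For the last row: SE = √(1/90 + 1/63) = 0.164, and 0.15/0.164 = 0.91. These figures ignore clustering and covariate adjustment. The last row takes f above the plan's whole attrition allowance of 25%, so it is an upper illustration.

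**6. Power.** If non-payers were not replaced, power under the variant in step 3 would fall from 79.5% to 77.4% at f = 10% and 74.7% at f = 20%. The issue is bias more than power.

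**The case against.** The strongest reply is that the article nowhere says a non-paying household is dropped. It commits to analysis by initial assignment and to data collection at the same time points for all participants. On the order in the Randomization section, the deposit can only be a step in taking up the share, which fits its stated purpose. The participant flow diagram (Fig. 1) is not shown in the text at hand and might settle the matter. This stands as far as it goes: a reader might infer that the intent-to-treat comparison is already broken, and the document does not support that. It would follow only if non-payers were excluded. But the enrolment list is a stated rule, not a missing detail, and followed as written it permits that exclusion.

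A second reply is that non-payment may be rare. Willingness to pay for the half-price share and to attend classes is screened before assignment in both arms, and the deposit is small and refundable. The planned models also adjust for the baseline outcome and covariates. These features may well keep f and the bias low, which is why the illustration starts near zero. They cannot be relied on to remove differences in unmeasured motivation.

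A reader might also infer that the intervention arm would look better as a result. Outcomes are changes from baseline, and no section shows that poorer or less engaged families would change less without the intervention. That direction is plausible, not established.

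Finally, a reader might see two conflicting moments for randomisation, since the section also says "Randomization will take place after informed consent is obtained at study enrollment appointments". There is no conflict: consent is given at the baseline visit, so both sentences put assignment after consent, and one adds that baseline assessment comes first. At most, it would help to state that the first online questionnaire precedes assignment.

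**Conclusion.** The enrolment list and the Randomization section contradict each other for the intervention arm, and the intent-to-treat set is left undefined for randomised households that do not pay. As written, the plan permits selection after randomisation in one arm only. That conclusion rests on the wording alone.

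Whether selection would occur, how large it would be and which way it would act cannot be determined from the document. Under the assumed values the unadjusted bias runs from 0.01 SD (negligible) to 0.15 SD, with type I error from about 5% to about 15%. Baseline adjustment may reduce it. The wording should be corrected before assignment starts, because households excluded and never followed cannot be recovered at analysis.

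**What to change.** - Define enrolment by steps that both arms complete before assignment: consent, baseline visit and first online questionnaire. Say explicitly that the questionnaire comes before assignment.
- Take the deposit out of the enrolment list and make it a condition of receiving the CO-CSA share. Stated willingness to pay already serves as the screening criterion in both arms.
- In the analysis section, define the intent-to-treat set as every randomised household, followed and analysed in its assigned arm whether or not it paid. Apply the same rule to the Year 3 recruits (Groups 3 and 4).
- Report the number of intervention households not paying, as non-adherence.

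The cost is a change of wording, continued follow-up of non-payers, and an estimated effect that may be slightly diluted by households that never took up the share.
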